## Abstract

**Background:**

Rifampicin-resistant tuberculosis (RR-TB) poses a great threat to global health. Increasing evidence of novel regimens in trial settings has risen, but the combinations of oral shorter regimens have not been optimised. An evaluation of the efficacy and safety of short-term regimens utilizing various drug combinations is essential across different settings.

**Methods:**

INSPIRE TB is a pragmatic, multicentre, randomised, controlled, non-inferiority open-label trial to evaluate novel regimens in pulmonary RR-TB patients of 16–75 years old with or without fluoroquinolone resistance. Before randomisation, an individualized assessment is conducted, considering drug susceptibility, contradictions, tolerance. Eligible participants are randomised based on fluoroquinolone susceptibility results from the Xpert MTB/XDR assay. Participants susceptible to fluoroquinolones are randomised to receive either one of seven different nine-month oral regimens or a nine-month standard-of-care regimen as the control. The experimental arms are five-drug regimens, each consisting of five agents selected from the following: bedaquiline, linezolid, a fluoroquinolone, cycloserine, clofazimine and pyrazinamide. Fluoroquinolone-resistant participants are randomised to either a 9-month oral regimen (bedaquiline, cycloserine, clofazimine, linezolid and pyrazinamide), or a 20-month conventional regimen as control in a 1:1 ratio. The primary outcome is the proportion of participants with a favourable outcome (two negative culture for *Mycobacterium Tuberculosis*, the latest sample collected between month 21 and 23) at 21 months after randomisation in the modified intention-to-treat population, measured in fluoroquinolone-susceptible and fluoroquinolone-resistant participants respectively. A sample size of 832 fluoroquinolone-susceptible RR-TB patients and 234 fluoroquinolone-resistant RR-TB patients afford 80% power to establish non-inferiority with a non-inferiority margin of 10% at a one-sided α level of 2.5%. The type I error will be controlled with a fixed-sequence approach.

**Discussion:**

Identifying safer and effective short regimens remains an obstacle for drug-resistant tuberculosis and more treatment options are needed to benefit patients from different countries and settings to reduce disease burden. The INSPIRE TB study hopes to provide robust evidence on various options of safer and effective 9-month oral regimens for RR-TB in China.

**Trail registration:**

ClinicalTrial.gov, NCT05081401. Registered on October 18, 2021; the record was lastupdated for study protocol version 6.0, on 06 April 2025.

**Supplementary Information:**

The online version contains supplementary material available at 10.1186/s12879-026-13017-y.

## Background

Rifampicin-resistant tuberculosis (RR-TB) is a growing public health threat, caused by *Mycobacterium Tuberculosis* (MTB) strains resistant to key first-line drugs. Globally, an estimate of 390,000 incident cases of multidrug-resistant or rifampicin-resistant tuberculosis (MDR/RR-TB) were reported in 2024, accounting for 3.2% of all TB cases [1–4]. Treatment of MDR/RR-TB requires regimens combining second-line or novel drugs. Although the global treatment success rate has gradually improved since 2012, it remained relatively low at 71% in 2022 [3].

Facing ongoing challenges in RR-TB treatment, the pursuit of shorter, safer, and more effective regimens remains a key research priority. In 2019, the landmark STREAM trial—the first randomised controlled trial evaluating shorter regimens for MDR-TB—demonstrated non-inferior efficacy of a standardised 9-month, seven-drug regimen compared to the longer regimen [5]. The subsequent Nix-TB trial reported a 90% treatment success rate using a 26-week regimen of bedaquiline, pretomanid and linezolid in patients with pre-extensively drug-resistant tuberculosis (Pre-XDR TB) [6]. Recent results from the STREAM stage 2 trial showed treatment success rates of 83% and 91% for a 9-month and a 6-month oral bedaquiline-containing regimens, respectively [7]. Additionally, the endTB trial tested four different 9-month oral regimens containing bedaquiline or delamanid, with success rates exceeding 80% [8]. Despite growing evidence supporting various RR-TB treatment options, it remains crucial to evaluate shorter oral regimens with various drug combinations across different settings.

Overall, the INSPIRE TB study represents the first multicentre, multi-arm randomised controlled trial in China designed to systematically evaluate the efficacy and safety of multiple oral shorter regimens for RR-TB, stratified by fluoroquinolone resistance. For fluoroquinolone-susceptible patients, seven 9-month oral regimens will be compared against a 9-month standardized regimen, while for fluoroquinolone-resistant patients, a 9-month bedaquiline-containing oral regimen will be compare with a conventional long regimen. Each experimental regimen consists of five drugs selected from the following agents: bedaquiline, linezolid, fluoroquinolones (moxifloxacin or levofloxacin), cycloserine, clofazimine and pyrazinamide. Additionally, the study will investigate a structured linezolid dose-adjustment strategy to determine its optimal dosing. It is expected that the INSPIRE TB trial will broaden the range of shorter, oral treatment options for patients with RR-TB.

## Methods

### Design

The INSPIRE TB study is a pragmatic, multicentre, randomised, controlled, open-label non-inferiority trial to evaluate the efficacy and safety of seven 9-month oral regimens compared to a 9-month standard of care (SOC) regimen in RR-TB participants susceptible to fluoroquinolones, and a bedaquiline-containing 9-month oral regimen compared to a 20-month conventional regimen in RR-TB participants resistant to fluoroquinolones (shown in Fig. 1).

**Fig. 1 Fig1:**
[figure not shown]
Study schematic. The INSPIRE TB study is a multicentre, open-label, randomised, pragmatic, non-inferiority trial recruiting rifampicin-resistant pulmonary tuberculosis patients aged 16–75 years old. Eligible participants will be divided into group **A** (fluoroquinolone susceptible) and group **B** (fluoroquinolone-resistant) according to the Xpert MTB/XDR assay. Recruitments of three experimental arms (A2b, A2c, A5) were ceased in protocol version 6.0 (Nov 2024). Abbreviations: RR-TB, rifampicin-resistant tuberculosis; FQ(S), fluroquinolone-susceptible; FQ(R), fluoroquinolone-resistant; SOC standard of care

### Setting

The INSPIRE TB study is a multicentre trial led by the National Medical Center for Infectious Diseases at Huashan Hospital, Fudan University. The study is being conducted across a nationwide network of over 40 clinical sites in China. Participating sites are selected with the following criteria: high burden of RR-TB; experience of treating drug-resistant TB; experience of managing adverse events during drug-resistant TB treatment; adequate supply of regimen drugs; laboratory equipped for microbiology culture and molecular diagnostics.

### Study regimens

#### In participants susceptible to fluoroquinolones

RR-TB patients susceptible to fluoroquinolones are identified with the Xpert MTB/XDR assay (Cepheid; Sunnyvale, CA, USA). Experimental arms are seven five-drug oral regimens composed of agents selected from the following: bedaquiline, linezolid, a fluoroquinolone (moxifloxacin or levofloxacin), cycloserine, clofazimine and pyrazinamide. Composition of the regimens are described in Table 1. All regimens contain pyrazinamide except for regimen A1 and regimen B-SOC. To minimize potential toxicity, each regimen includes no more than two major QT-prolonging drugs (bedaquiline, clofazimine and moxifloxacin). Treatment duration of the experimental arms is 9 months. A 2-month extension of treatment is allowed with the presence of cavities at month 9 or in case of a positive culture at month 2. Baseline molecular drug susceptibility test (DST) of pyrazinamide will be performed using the whole gene sequencing (WGS) technique. The result of pyrazinamide molecular DST will be interpreted by technical staff at central laboratory of Huashan Hospital, Fudan University according to criteria published previously [9, 10]. Once a participant is proved resistant to pyrazinamide by WGS results obtained at baseline, pyrazinamide will be discontinued with no need for extra drug replacement.

The control regimen for fluroquinolone-susceptible participants is the current SOC regimen recommended by the national guidelines [11]. The SOC regimen comprises 1–2 drugs from group A (bedaquiline, linezolid, moxifloxacin or levofloxacin) and a drug from group B (clofazimine, cycloserine) along with ethambutol, pyrazinamide and high-dose isoniazid. Composition of the study regimen and dosing is described respectively in Tables 1 and 2. Treatment duration is 9 months in total, including a 4-month intensive phase and a 5-month continuation phase. The intensive phase could be extended to 5 months or 6 months if smear conversion has not occurred by month 4 or month 5.

**Table 1 Tab1:** Description of trial regimens

Group		Regimen	Duration (month)	Status
FQ(s)^a^	A-SOC	4 Bdq (Lzd) + Lfx (Mfx) + Cfz (Cs) + Pto + E + H_h_ + Z/5Lfx (Mfx) + Cfz (Cs) + E + Z	9	Recruiting
	A1	Bdq + Lfx (Mfx) + Lzd + Cs + Cfz	9	Recruiting
	A2a	Bdq + Mfx (Lfx) + Lzd + Cs + Z	9	Recruiting
	A2b	Bdq + Mfx (Lfx) + Lzd^b^ (2 months) + Cs + Z	9	Closed following protocol amendment
	A2c	Bdq + Mfx (Lfx) + Lzd^c^ + Cs + Z	9	Closed following protocol amendment
	A3	Bdq + Lfx (Mfx) + Lzd + Cfz + Z	9	Recruiting
	A4	Bdq + Lfx (Mfx) + Cfz + Cs + Z	9	Recruiting
	A5	Mfx (Lfx) + Lzd + Cfz + Cs + Z	9	Closed following protocol amendment
FQ(r)	B-SOC	6Bdq + Lzd + Cs + Cfz /14Lzd + Cs +Cfz	20	Enrolment completed
	B1	Bdq + Lzd + Cs + Cfz + Z	9	Enrolment completed

Abbreviations: Bdq, bedaquiline; Cfz, clofazimine; Cs, cycloserine; Lzd, linezolid; Mfx, moxifloxacin; Lfx, levofloxacin; Z, pyrazinamide; H_h_, high-dose isoniazid; E, ethambutol; Pto, prothionamide; FQ(s), fluroquinolones susceptible; FQ(r), fluroquinolones resistant

^a^ Drug susceptibility of fluroquinolones is determined with Xpert MTB/XDR

^b^ Treatment duration of linezolid is 2 months in regimen A2b

^c^ Treatment duration of linezolid is 9 months and dose of linezolid is halved after 2 months in regimen A2c

**Table 2 Tab2:** Regimen drug doses by weight bands and usage

Drug	Weight band (kg)		Usage
	30–50 kg (mg/d)	> 50 kg (mg/d)	
Bedaquiline	400 mg daily for 2 weeks and then 200 mg three times a week		With meal
Linezolid ^a^	600 mg		Once daily, before or after meal
Moxifloxacin	400 mg		Once daily, before or after meal
Levofloxacin	500 mg	750 mg	Once daily, before or after meal
Clofazimine	100 mg		Once daily, before or after meal
Cycloserine	500 mg	750 mg	Once or divided in two doses, before or after meal
Pyrazinamide	1500 mg		Once daily, before or after meal
Prothionamide	500 mg	750 mg	Once or divided in two doses, before or after meal
Ethambutol	750 mg	1000 mg	Once daily, before or after meal
Isoniazid	400 mg	600 mg	Once daily, before or after meal

^a^ In regimen A2b, treatment dosage and duration of linezolid is 600 mg for 2 months. In regimen A2c, linezolid is routinely modified to 300 mg daily after 2 months of treatment and remains the same dose in subsequent treatment

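### The stated limit of two major QT-prolonging drugs per regimen conflicts with the bracketed moxifloxacin option that Table 1 lists for A1, A3 and A4

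*Protocol article*

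**What the plan says.** In the protocol article, under Study regimens, the subsection on fluoroquinolone-susceptible participants gives a reason of limiting toxicity and then states that "each regimen includes no more than two major QT-prolonging drugs (bedaquiline, clofazimine and moxifloxacin" being the drugs meant. The sentence carries no exception. The same paragraph gives the components available to the experimental arms, including "a fluoroquinolone (moxifloxacin or levofloxacin), cycloserine, clofazimine and pyrazinamide", and attaches no arm-specific condition to the choice of fluoroquinolone.

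Table 1, in the same subsection, gives these compositions:

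- A1: "Bdq + Lfx (Mfx) + Lzd + Cs + Cfz"
- A3: "Bdq + Lfx (Mfx) + Lzd + Cfz + Z"
- A4: "Bdq + Lfx (Mfx) + Cfz + Cs + Z"
- A2a, for comparison: "Bdq + Mfx (Lfx) + Lzd + Cs + Z"
- A-SOC, start of the intensive phase: "4 Bdq (Lzd) + Lfx (Mfx) + Cfz (Cs) + Pto + E", followed by high-dose isoniazid and pyrazinamide

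The footnotes to Table 1 deal with how fluoroquinolone susceptibility is determined and with linezolid in A2b and A2c. None explains the brackets or restricts the use of the bracketed drug.

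On the control, the prose says "The SOC regimen comprises 1–2 drugs from group A", adds one group B drug, and then lists ethambutol, pyrazinamide and high-dose isoniazid. It does not mention prothionamide.

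**The concern.** The limit is presented as a safety property of the regimens. In A1, A3 and A4, two of the three counted drugs are fixed, so the limit depends entirely on which fluoroquinolone is used, and the table offers the one that breaks it. Someone working from the table and someone working from the sentence could treat the same participant differently, each with support from the article.

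These arms are still enrolling across more than 40 sites. QTc prolongation of grade 3 or above, and permanent stopping or replacement of a drug because of QTc prolongation, are both secondary outcomes. What these arms may contain therefore bears on participant safety and on how those results are described.

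**Working it through.** This is a count, not a power or error-rate calculation.

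**Inputs.** The counted set is bedaquiline (Bdq), clofazimine (Cfz) and moxifloxacin (Mfx), from the sentence stating the limit. The compositions are from Table 1. The bracketed drug is read as the alternative to the drug before it; the article does not define the brackets, so this is an assumption, though the prose offers either fluoroquinolone.

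**Step 1: the stated figure, using only first-listed drugs.** A1, A3, A4 and the A-SOC intensive phase each contain Bdq and Cfz with levofloxacin: 2. A2a, A2b and A2c contain Bdq and Mfx: 2. A5 contains Mfx and Cfz: 2. B-SOC and B1 contain Bdq and Cfz: 2. On this reading the stated maximum of two is reproduced in every regimen.

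**Step 2: every combination that Table 1 lists.**

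| Regimen | Combinations | Maximum count | Combinations with 3 |
|---|---|---|---|
| A1 | 2 | 3 | 1 |
| A3 | 2 | 3 | 1 |
| A4 | 2 | 3 | 1 |
| A-SOC, intensive phase | 2 × 2 × 2 = 8 | 3 | 1 |
| A-SOC, continuation phase | 2 × 2 = 4 | 2 | 0 |
| A2a, A2b, A2c | 2 each | 2 | 0 |
| A5 | 2 | 2 | 0 |
| B-SOC, intensive phase | 1 | 2 | 0 |
| B1 | 1 | 2 | 0 |

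In A1, A3 and A4 the count is Bdq (1) + Cfz (1) + Mfx (1) = 3 whenever the bracketed fluoroquinolone is chosen. In A-SOC it reaches 3 only when Bdq is taken over linezolid, Mfx over levofloxacin and Cfz over cycloserine, all together. The A-SOC continuation phase has no bedaquiline.

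**Step 3: size.** The section on sample size sets 104 per arm and a revised Group A total of 520 (5 × 104). The three arms with a direct conflict have a target of 3 × 104 = 312, and 312 / 520 = 60%. The article does not report how many participants receive moxifloxacin, so the number actually given three of these drugs cannot be derived and could be anywhere from none upwards.

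**Step 4: composition of A-SOC, prose against tables.** Table 1 lists prothionamide in the intensive phase, Table 2 gives it a dose row, and Table 3 schedules monthly thyroid tests for those taking it. The prose leaves it out. The prose range of one to two group A drugs includes the two that Table 1 shows, so there is no conflict on that count.

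**The case against.** The strongest reply is that the table was laid out with the limit in mind. Levofloxacin comes first wherever bedaquiline and clofazimine can coincide (A-SOC, A1, A3, A4), and moxifloxacin comes first where they cannot (A2a to A2c, A5). The limit could then be read as silently restricting the bracketed option. The article is also a condensation: sites work from protocol version 6.0, and the individualised assessment before randomisation is detailed in supplementary material; neither is shown here, and either may settle the choice. Monthly electrocardiograms during treatment and review by the data and safety monitoring board are further safeguards.

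Much of this stands. The ordering makes an intended default plausible, and a reader who infers that following Table 1 necessarily breaches the limit goes too far. But an order of listing is not a restriction, and the article states both the limit and the option without linking them. The safeguards do not say which fluoroquinolone may be used in these arms.

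Other stronger readings are also unsupported:

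- *A-SOC is affected to the same degree, making 4 × 104 = 416.* The limit sits in the paragraph on the experimental arms, and the control has its own paragraph with no such limit. The wording does refer to each regimen, and the sentence before it names B-SOC, so whether A-SOC is covered is unclear. Only one of eight combinations reaches three.
- *The contradiction confounds the QTc comparisons.* Choice of fluoroquinolone is open in every Group A arm, including A2a, where no combination exceeds two. Any such effect comes from the pragmatic design, not from this mismatch.
- *The omission of prothionamide changes primary-outcome classification.* The relevant item under permanent regimen change in Table 4 requires two or more drugs to be added or replaced. One drug missing from the prose does not by itself meet it, and no other route to misclassification is evident.

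**Conclusion.** The point holds as an internal contradiction in A1, A3 and A4: an unqualified limit of two, against a listed option that always gives three. It concerns the permitted alternative, not the first-listed drugs, which respect the limit throughout.

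The three arms account for 312 of the 520 Group A target. This is the planned enrolment in arms where the option exists and must not be read as a number exposed. A-SOC joins them only if the limit is meant to cover the control. The conclusion assumes that brackets mean an alternative and that the article represents what sites follow; if the full protocol or supplement already restricts the option, the defect lies in the article alone.

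The prothionamide omission is a minor mismatch between text and tables. The documents do not settle which clinical statement is correct, and no view is taken here.

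**What to change.** 1. Reconcile the sentence on the QT-drug limit with the bracketed moxifloxacin option in the A1, A3 and A4 rows of Table 1, and define what the brackets mean. The clinical leads decide which statement stands.
2. State whether the limit applies to A-SOC.
3. Bring the prose description of A-SOC into line with Tables 1 to 3 on prothionamide.
4. Give all sites one consistent version.
5. Optionally, tabulate the two QTc outcomes by fluoroquinolone actually received within each arm. The section on treatment compliance says that drug types are verified and entered in the case report form, so no new data are needed. The table would be descriptive, since this choice is not randomised.

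The cost is a protocol clarification and a site notice, plus one extra table if item 5 is adopted. Sample size, randomisation and the primary analysis are unaffected.

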#### In participants resistant to fluoroquinolones

Pre-XDR TB participants are identified with the Xpert MTB/XDR assay prior to treatment initiation. The experimental arm is a 9-month regimen consisting of bedaquiline, cycloserine, clofazimine, linezolid and pyrazinamide. Treatment could be extended to 11 months if cavities are present at month 9 or in case of a positive culture at month 2. Pyrazinamide will be discontinued from the study regimen if baseline WGS results reveal pyrazinamide resistance.

The comparator is a conventional longer regimen consistent with the national guidelines [11], including bedaquiline, cycloserine, clofazimine and linezolid. Treatment duration is 20 months, with a 6-month intensive phase and a 14-month continuation phase. Composition of the study regimen and dosing is described respectively in Tables 1 and 2.

#### Eligibility criteria

Participants eligible for the INSPIRE TB study must fulfil all inclusion criteria:

Male or female participants aged 16–75 years old, with weight over 30 kg, regardless of HIV status.Pulmonary TB with rifampicin resistance diagnosed with either phenotype DST (obtained within 60 days prior to randomisation) or World Health Organization (WHO)-approved rapid molecular diagnostic testing [12].Signed informed consent form (ICF).

Participants will be excluded from the trial if they meet any of the following criteria:

Participants with known allergies, hypersensitivity, or contraindication to any of the study drugs as described in the Supplementary material.Participants with central nervous system TB, tuberculous osteomyelitis and arthritis, or hematogenous disseminated pulmonary TB.Participants known to be pregnant or breastfeeding at the time of enrolment.Participants who have received second-line anti-TB drugs for more than 14 days prior to randomisation, including bedaquiline, moxifloxacin, levofloxacin, linezolid, cycloserine and clofazimine.Participants in critical condition and with a physician-estimated survival of less than 3 months.

#### Recruitment process

RR-TB patients diagnosed with molecular or phenotypic DST are identified by investigators and clinical staff at research sites. Investigators then explain the study regimens and follow-up schedule, as well as potential risks and benefits to participants who agree to eligibility assessment. After fully informed consent, participants are involved in the screening process, including collection of medical history and personal information, physical examination and baseline clinical evaluation. Participants who meet the eligibility criteria are included in the trial and the Xpert MTB/XDR assays are performed to determine fluoroquinolone susceptibility.

#### Randomisation

Randomisation is based on an online system (REDCap) operated remotely at Huashan Hospital, Fudan University and is stratified by research sites. Prior to randomisation, patient eligibility is re-confirmed through a comprehensive review of medical history. An individualized eligibility assessment was documented in the electronic case report form, capturing detailed data on drug susceptibility, contraindications, concomitant medications, and treatment tolerance, as specified in the Supplementary Materials. Patients with known resistance or contraindications to regimen components are excluded from the randomisation procedure and receive guideline-based standard care. Eligible participants will be stratified into fluroquinolone-susceptible arms (group A) and fluoroquinolone-resistant arms (group B) based on baseline Xpert MTB/XDR results.

In group A, the randomisation ratio between the regimen A-SOC and each experimental arm is 1:1. Enrolment into the experimental arm will be ceased once its planned sample size is reached. Participants resistant to fluoroquinolones are randomised to regimen B1 and regimen B-SOC in a 1:1 ratio.

In response to updated RR-TB treatment guidelines and emerging evidence, this trial was strategically optimized in 2024. The initial design included a bedaquiline-free arm (regimen A5). Following WHO’s endorsement of bedaquiline-based oral shorter regimens [13, 14], the study protocol was amended in version 6.0 (November 2024) to discontinue the enrolment of regimen A5, ensuring sufficient sample size for evaluation of bedaquiline-containing arms. In addition, randomisations to regimen A2b and A2c were halted based on two primary considerations. First, a recently published multicentre randomised controlled trial demonstrated the non-inferior efficacy of a nearly identical structured linezolid dose-reduction strategy [15], thereby compromising the novelty of our pre-planned analysis. Second, enrolment has progressed more slowly than we initially anticipated. Therefore, a strategic decision was made to concentrate limited resources to prioritize the remaining arms to address critical evidence gaps in RR-TB treatment.

